### Statistical analysis plan

We prespecify the following primary endpoints: [1] overall survival from registry enrolment; [2] organ-specific progression (e.g., incident heart failure, renal failure) defined by laboratory, imaging, and electrophysiological standard clinical criteria (e.g., N-terminal pro B-type natriuretic peptide or reduction of ejection fraction in echocardiography for heart failure, creatinine clearance for renal failure, neurofilament light chains and nerve conduction studies for neuropathy progression, and further as detailed in the subtype-specific sections in the Study Protocol); and [3] longitudinal quality-of-life scores. Secondary endpoints include subtype-specific trajectories and treatment-specific outcomes. Survival endpoints will be calculated using Kaplan–Meier and Cox models; when competing risks are relevant (e.g., cause-specific events), Fine–Gray models will be used. Longitudinal continuous outcomes (biomarkers, PROMs) will be analysed with linear mixed-effects or generalised estimating equations. For comparative effectiveness questions, we will adjust for confounding using multivariable regression and propensity score methods (matching/weighting); the a priori covariate set includes age, sex, subtype, baseline stage/organ involvement, and key comorbidities (DAG-informed).

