Missing data will be addressed by multiple imputation by chained equations (MICE) under a MAR assumption; results will be pooled with Rubin’s rules and compared with complete-case analyses in sensitivity checks. We control multiplicity for primary endpoints (e.g., Holm/Bonferroni) with α = 0.05 (two-sided). Interim analyses are descriptive only. Based on current referral volumes, we anticipate enrolment of ~20–30 patients/year; over five years (N ≈ 100–150), precision for a 10% event rate is ±~6% (95% CI). Analyses will be performed in R; code and analysis manifests will be shared with the de-identified data release. To address time-dependent exposures, treatment status will be modelled as a time-varying covariate using episode splitting, in which each patient’s follow-up is partitioned into consecutive intervals reflecting their actual exposure status at each point in time. Immortal-time bias will be addressed by classifying all person-time prior to treatment initiation as unexposed, ensuring that the pre-treatment observation window is not misattributed to the treated state. Since treatment switches most commonly occurr in the context of clinical progression, they will be handled by opening a new interval at the date of the switch, with exposure updated accordingly to reflect the new treatment, while prior intervals retain their original classification. Treatment discontinuation will be handled analogously, with patients reclassified as unexposed from the discontinuation date onward. Where dose-level data are available, dose changes will be treated by the same mechanism.

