We acknowledge two limitations inherent to a routine-care registry setting. First, treatment event dates are recorded at clinical visits rather than to the exact calendar day; interval boundaries therefore carry a degree of temporal imprecision. Second, the frequency and timing of follow-up visits are clinically driven rather than protocol-fixed, which may result in treatment changes between visits not being captured with full precision. To quantify the potential impact of the first limitation, a sensitivity analysis applying a ± 4-week uncertainty window around documented treatment event dates will be conducted. As a further sensitivity analysis, a landmark approach will be applied at 6 and 12 months, classifying patients by treatment status at the landmark and restricting follow-up accordingly; as this approach avoids immortal-time bias by design rather than by statistical adjustment, convergence of results with the primary analysis will serve as an indicator of robustness. Given these constraints, comparative effectiveness estimates derived from time-dependent Cox proportional hazards models should be interpreted as exploratory and hypothesis-generating rather than causal.

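### Fine–Gray is prescribed for competing risks without limits and is not reconciled with the time-varying Cox models for treatment, so the model for treatment effects on organ progression is left open

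*Protocol article*

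**What the plan says.** All the relevant text is in the Statistical analysis plan section of the protocol article.

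- The second primary endpoint is "organ-specific progression (e.g., incident heart failure, renal failure" and similar events. Treatment-specific outcomes are listed as secondary.
- The general rule is "Survival endpoints will be calculated using Kaplan–Meier and Cox models". The exception is "when competing risks are relevant (e.g., cause-specific events), Fine–Gray models will be used". No other competing-risk model is named.
- For exposure, "treatment status will be modelled as a time-varying covariate using episode splitting". The section adds that "treatment switches most commonly occurr in the context of clinical progression", and it handles stopping treatment "with patients reclassified as unexposed from the discontinuation date onward". It gives no rule for exposure after death.
- On interpretation, "comparative effectiveness estimates derived from time-dependent Cox proportional hazards models should be interpreted as exploratory and hypothesis-generating rather than causal".
- As a sensitivity analysis, "a landmark approach will be applied at 6 and 12 months, classifying patients by treatment status at the landmark".

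**The concern.** Death prevents any later organ progression, so the competing-risk exception reaches the second primary endpoint. Read literally, it selects Fine–Gray for every regression on that endpoint, including one with treatment as a covariate. The closing statement on comparative effectiveness points to Cox instead, but does not say whether death is censored as a competing event or whether a companion model for death is reported.

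The choice matters for two reasons.

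1. Fine–Gray keeps patients who have died in the risk set for progression. Treatment status that follows the patient's own course has no value after death, so the analyst must invent one.
2. Even when treatment is fixed, the subdistribution hazard ratio responds to effects on death. A treatment that only prolongs life leaves patients more time to progress, and its ratio for progression rises above 1.

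Two analysts following this section could therefore report different quantities for the same treatment and endpoint, possibly pointing in opposite directions.

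**Working it through.** **The plan's own figure.** The only figure for sample size is a precision of about ±6 points for a 10% event rate. It reproduces at N = 100: 1.96 × √(0.10 × 0.90 / 100) = 5.9 points. It has no bearing on this point. The documents give no progression, death or treatment-start rates, so every rate below is an assumption.

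**Step 1: fixed treatment, by hand.** With constant hazards λ₁ (progression) and λ₂ (death), cumulative incidence at time t is

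CIF(t) = λ₁/(λ₁+λ₂) × [1 − exp(−t(λ₁+λ₂))].

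Assume λ₁ = 0.15/year in both groups, so the cause-specific hazard ratio is 1.00, and t = 5 years.

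- Untreated, λ₂ = 0.20: (0.15/0.35) × [1 − exp(−1.75)] = 0.354.
- Treated, λ₂ = 0.10: (0.15/0.25) × [1 − exp(−1.25)] = 0.428.
- Approximate subdistribution hazard ratio: ln(1 − 0.428) / ln(1 − 0.354) = 1.28.

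**Step 2: a range of death rates, fixed and time-varying treatment.** This is a simulation of 400,000 patients with 5 years of follow-up and administrative censoring only. Progression is 0.10/year, and death is 0.05, 0.15 or 0.30/year before any treatment effect. In the time-varying runs treatment starts at 0.5/year. Entries are estimated hazard ratios for progression.

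| True effect of treatment | Model and coding | Death 0.05 | 0.15 | 0.30 |
|---|---|---|---|---|
| None on progression or death | Fine–Gray, exposure frozen at death | 1.21 | 1.50 | 1.77 |
| | Fine–Gray, unexposed after death | 1.53 | 2.35 | 3.26 |
| | Fine–Gray, exposure continued hypothetically | 1.00 | 1.00 | 1.00 |
| None on progression, 0.5 on death | Fine–Gray, exposure frozen at death | 1.25 | 1.67 | 2.18 |
| | Fine–Gray, exposure continued hypothetically | 1.03 | 1.10 | 1.18 |
| | Fine–Gray, treatment fixed at baseline | 1.06 | 1.20 | 1.36 |
| 0.7 on progression, 0.5 on death | Fine–Gray, exposure frozen at death | 0.89 | 1.20 | 1.58 |

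A cause-specific Cox model with the same treatment coding gave 0.99 to 1.01 when the truth was 1.0 and 0.70 to 0.71 when it was 0.7, in every scenario.

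**Step 3: reading the results.** When treatment does nothing, the Fine–Gray estimate depends on the post-death coding. With frozen exposure, patients who die before starting treatment stay in the untreated risk set and dilute the untreated event rate. Only hypothetically continued exposure removes this, and it cannot be observed. The rule that makes patients unexposed after stopping treatment would, if extended to death, give the most distorted of the three codings. With no effect on either outcome and death at 0.15/year, changing the treatment-start rate between 0.2 and 2.0/year moved the frozen-exposure ratio between 1.37 and 1.71.

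Fixing treatment status removes the coding problem but not the mixing with death, as Step 1 and the fixed-treatment row show. The same mixing would affect the 6- and 12-month landmark analyses if they were run with Fine–Gray.

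**The case against.** The strongest reply is that the section already names the model for treatment comparisons. Its closing statement ties these estimates to time-dependent Cox models and labels them exploratory, and nothing expressly puts time-varying treatment into a Fine–Gray model. A reader might infer that the plan will report ill-defined treatment hazard ratios. The text does not support that; it leaves the possibility open.

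Other parts of the reply also stand.

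- Treatment-specific outcomes are secondary, so it would be wrong to say that a primary treatment comparison is compromised. Primary status belongs to the progression endpoint itself.
- The phrase about cause-specific events can be read as an example of where competing risks arise. It does not promise to estimate cause-specific hazards, so it does not contradict Fine–Gray.
- A subdistribution hazard ratio of 1.28 is not an error in itself. It correctly describes cumulative incidence, which is a different question from the effect on the rate of progression.
- Fine–Gray is acceptable for prognosis by baseline subtype or stage.
- The landmark analyses fix exposure and so avoid the post-death coding problem.

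It can also be argued that a journal article leaves the choice of hazard model to a fuller plan. That does not dispose of the point. The article itself states an unrestricted rule and then names a different model for treatment comparisons, without saying which governs progression when death competes. The exploratory label concerns causal interpretation and does not settle which model applies.

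**Conclusion.** The point holds as an unreconciled prescription, not as a demonstrated misanalysis. The Fine–Gray rule covers organ progression with competing death and has no restriction on covariates. Treatment is time-varying and driven by the patient's course. The Cox statement does not say how competing death is treated.

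If the Fine–Gray rule were followed for treatment effects, the estimate would depend on an arbitrary coding after death and would absorb effects on death. Under the assumed rates, a treatment with no effect on either outcome gives ratios from 1.21 to 3.26 across the two codings an analyst could actually apply. A fixed treatment that only halves mortality gives 1.06 to 1.36 in the simulation and 1.28 in the hand calculation. These sizes depend on the assumed constant hazards and treatment-start rates. That the result depends on coding follows from how the risk set is built, provided some patients die before progression. The mixing also requires an effect of treatment on death.

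**What to change.** Amend the Statistical analysis plan section to state three things.

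1. Treatment effects on organ progression are estimated with cause-specific Cox models using episode splitting, with death censored as a competing event. The matching cause-specific model for death is reported alongside. The same applies to the landmark analyses, with treatment status fixed at the landmark.
2. Absolute risk of progression is shown with Aalen–Johansen cumulative incidence curves.
3. Fine–Gray is limited to prognostic or absolute-risk models with covariates fixed at baseline.

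This takes a few sentences, uses standard R survival functions and needs no new data. The downside is one additional model to report per endpoint.

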### Study status

Ongoing (study start: 03.04.2020; study duration: at least 10 years; end date: 03.04.2030 or later; expected completion of participant recruitment: 2030 or later, expected results from study: 2030 and earlier for sub-study results). On March 31^st^ 2026, recruitment included a total of 849 patients.

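### The stated accrual of 20–30 patients per year and N ≈ 100–150 conflict with the 849 patients already recruited, so the ±~6% precision does not describe this registry and is roughly 1.5 to 3 times too wide

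*Protocol article*

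**What the plan says.** The Statistical analysis plan section gives the article's only statement on size and precision. It sets a rate, derives the size from it, and then the precision: "we anticipate enrolment of ~20–30 patients/year; over five years (N ≈ 100–150), precision for a 10% event rate is ±~6% (95% CI"). It presents the rate as resting on present referral numbers. The same section uses a two-sided α of 0.05, which matches a 95% interval.

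The Study status section gives the calendar: "study start: 03.04.2020; study duration: at least 10 years; end date: 03.04.2030 or later". It expects recruitment to continue to 2030 or later. It also gives the count at 31 March 2026: "recruitment included a total of 849 patients".

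Two other sections bear on how many of those patients can be analysed. The inclusion criteria admit clinically suspected cases and people with a genetically confirmed TTR mutation, as well as histologically or scintigraphically diagnosed patients. The discontinuation criterion ends observation once amyloidosis has been excluded. The article does not say how many patients left for that reason.

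**The concern.** Both statements are current text in one article. The planning sentence is in the present tense and claims to rest on present referral numbers. Five years from the study start ended in April 2025, about a year before the 849 count was taken. A reader who takes the planning sentence at face value would think the registry holds, or will hold, 100 to 150 patients. It has recruited several times that number.

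What is at stake is the reader's picture of what the registry can estimate. The precision statement is the only one offered, and it belongs to a cohort of a different size. Anyone judging the feasibility of an external data request, or reading later results against this plan, has two incompatible sample sizes to choose from.

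**Working it through.** **Inputs.** From Statistical analysis plan: 20–30 patients per year, five years, event rate p = 0.10, 95% confidence, stated half-width about 6 points. From Study status: start 3 April 2020, 849 recruited by 31 March 2026, duration at least 10 years.

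**1. The plan's own figure.**
- Size: 20 × 5 = 100 and 30 × 5 = 150, as stated.
- Half-width = 1.96 × √(p(1 − p)/N) = 1.96 × √(0.09/N).
- N = 100: 1.96 × 0.0300 = 5.88 points (Wilson interval: 5.96).
- N = 125: 5.26 points.
- N = 150: 4.80 points.

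The stated ±~6% is reproduced at the lower end of the range. Quoting the conservative end with an approximation sign is ordinary practice and is not an error.

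**2. Observed accrual.**
- 3 April 2020 to 31 March 2026 is 2,188 days; 2,188/365.25 = 5.99 years.
- 849/5.99 = 141.7 patients per year.
- 141.7/30 = 4.7 and 141.7/20 = 7.1, so the observed rate is 4.7 to 7.1 times the stated one.
- At the stated rate, 20 × 5.99 = 120 to 30 × 5.99 = 180 patients would have been enrolled by that date.

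**3. Precision at the numbers the registry may have.** The number evaluable is not given, so the second and third rows are assumptions that show the range. The last column sets the stated 6 points against each result.

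| Evaluable patients | N | Half-width (points) | 6 ÷ half-width |
|---|---|---|---|
| All recruited | 849 | 2.02 | 2.97 |
| Half (assumed) | 425 | 2.85 | 2.1 |
| A quarter (assumed) | 212 | 4.04 | 1.5 |

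At N = 849 the Wilson interval is 8.2% to 12.2% and the Clopper–Pearson interval 8.1% to 12.2%, so the choice of interval hardly matters. Against the exact half-widths at N = 100 and N = 150, rather than the rounded 6, the ratios at N = 849 are 5.88/2.02 = 2.9 and 4.80/2.02 = 2.4.

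**4. Could exclusions explain the gap?** To bring 849 down to the 120–180 implied by the stated rate, only 120/849 = 14% to 180/849 = 21% of recruited patients could count. No section says this. The planning sentence also speaks of enrolment, which is the quantity the status section reports.

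**5. Projection, assuming constant accrual.** 141.7 × 10 = 1,417 patients by April 2030, with half-width 1.96 × √(0.09/1,417) = 1.56 points. The article does not state that accrual will stay constant.

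**The case against.** The strongest defence is that the error is harmless in direction. The registry is larger and more precise than the sentence says. The figure illustrates precision; it is not a power calculation, a recruitment cap or a stopping target. Interim analyses are descriptive, comparative-effectiveness estimates are declared exploratory, and the true count is printed elsewhere in the article. All of this stands, and it limits the severity.

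A second defence is that the sentence is an old forecast. The Study design section dates the protocol to version 1 of March 2020, so 20–30 per year may simply never have been updated. That is plausible, but nothing labels it as historical, and the sentence presents its basis as current.

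Several stronger readings are tempting, and the documents do not support them:
- A reader might infer a fixed threefold error. That needs all 849 to be evaluable, and the eligibility and discontinuation rules make this uncertain.
- A reader might infer that the five-year horizon is itself wrong. The registry has a "study duration: at least 10 years", but a five-year horizon can be an intermediate one, and sub-study results are expected before 2030.
- A reader might infer that covariate or subtype choices were sized to the wrong N. The covariate set is described as fixed in advance and informed by causal diagrams, and no section ties subtype analyses to 100–150 patients.
- A reader might fault the absence of subtype-level precision. A condensed article commonly leaves that to the full protocol or analysis plan.

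**Conclusion.** The mismatch is certain: about 142 patients per year observed against 20–30 stated, and 849 recruited against N ≈ 100–150, with no reconciling text. The accrual input and the N that follows from it are wrong as written. The half-width is correct for about 100 patients but is attached to the wrong cohort.

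For a 10% event rate the stated precision is roughly 1.5 to 3 times too wide. The upper end assumes that every recruited patient is evaluable; the lower end assumes that a quarter are. This is an internal inconsistency of moderate severity, not a calculation mistake and not a loss of power.

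**What to change.** Take either of two routes in the Statistical analysis plan section.

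1. Replace the sentence with observed accrual (849 patients at 31 March 2026, about 142 per year) and give the 95% half-width at the number of evaluable, confirmed patients. If that number were 849, the half-width would be ±2.0 points for a 10% event rate.
2. Keep the old figures, label 20–30 per year and N ≈ 100–150 as the original planning assumption, now superseded, and print the updated N and half-width beside them.

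In both cases, state whether N counts everyone recruited or only confirmed cases. If a projection to 2030 is wanted (about 1,400 patients, ±1.6 points), mark it as assuming constant accrual and all patients evaluable.

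The cost is one database count and a reworded sentence. No patients, visits or procedures are added.

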## Methods and analysis

### Study setting

The interdisciplinary Amyloidosis Registry is hosted by the Charité – Universitätsmedizin Berlin and embedded in the specialised Amyloidosis Center Charité Berlin (ACCB), which encompasses several medical specialties, including neurology, cardiology, hematology-oncology, nephrology, gastroenterology, radiology, nuclear medicine and ophthalmology. The study was approved by local ethical committee of the Charité – Universitätsmedizin Berlin and was registered under the identifier DRKS00032002 at the German Registry of Clinical Studies (DRKS – Deutsches Register Klinischer Studien). Participants are recruited via the ACCB outpatient clinic as well as from referring physicians with suspected or confirmed diagnosis of amyloidosis. Referring physicians are openly invited to present cases at the ACCB case conference (contact via [contact]) and scheduled for study inclusion and data collection in the corresponding ACCB specialty outpatient clinic. The study is purely observational and collects longitudinal data from patients with amyloidosis or suspected amyloidosis (until exclusion of amyloidosis). Primary presentation of patients with amyloidosis requires the identification of [1] organ manifestation, [2] amyloid type, and [3] therapeutic approach. Since many types of amyloidosis can affect several different organ systems, patients may present at different specialists, which can impose challenges in the structured documentation and continuation of workflow. To address this, patient cases are discussed in weekly case conferences in an interdisciplinarity fashion, always including at least one specialised cardiologist, neurologist, and hematologist, as well as a nuclear medicine specialist, and specialists depending on the respective organ manifestation of patients discussed. In the case conference, the diagnosis is either confirmed and treatment as well as follow-up procedure depending on the respective diagnosis decided, or further diagnostics and a new case conference are planned.

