### Eligibility criteria

#### Inclusion criteria.

1. Age ≥ 18 years2. Patients with suspected or diagnosed amyloidosis (any of the below)a. Clinically suspected diagnosis resulting from imaging or laboratory parametersb. Histomorphological diagnosis of amyloidosis or positive DPD scanc. Genetically confirmed TTR mutation3. Voluntary signing of informed consent (including opt-in options for collection of biological specimens)

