#### Exclusion criteria.

1. Age < 18*2.* Lack or inability for voluntary signing of informed consent

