### Study Protocol

This study aims at understanding real-world disease course, treatment effects, and quality of life of patients affected with systemic amyloidosis in an interdisciplinary setting. In order to achieve a broad understanding of organ involvement and outcomes, system-specific outcome measures were chosen to record longitudinal patient data dependent on organ involvement. For each specialty, we defined a standardised dataset to enable research and further collaboration efforts depending on the diagnosis. Although patients may present at any discipline when amyloidosis is first suspected, all patients undergo detailed cardiology and neurology examinations. Within the cardiology and neurology departments, informed written consent is obtained, and patients are enrolled in the registry study using a web-based database (Tbase) [8], that has been modified to reflect the needs of the ACCB. Tbase has been established, facilitating the easy entry of key data. This includes basic information such as demographics, height, weight, (suspected) diagnosis, (primary) organ manifestation, and therapy. Additionally, structured medical history and examination data are documented digitally and numerically to enable structured data analysis. Laboratory, imaging, and other ancillary data are automatically integrated from the hospital information system. Fig 1 presents an overview of enrolment and study visits.

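### Comparative effectiveness does not handle patients already on treatment at enrolment, its landmark check cannot reveal the resulting survivor bias, and subtype enters only as a covariate

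*Protocol article*

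**What the plan says.** All references are to the protocol article.

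- **Who enters.** Under Inclusion criteria the registry takes "Patients with suspected or diagnosed amyloidosis". Under Exclusion criteria the only bars are age below 18 and "Lack or inability for voluntary signing of informed consent". Study setting adds that "Participants are recruited via the ACCB outpatient clinic as well as from referring physicians with suspected or confirmed diagnosis of amyloidosis". Prior or current therapy is not a criterion anywhere. Under Study Protocol, therapy is one of the basic items entered in the database.
- **When the clock starts.** The Statistical analysis plan measures overall survival from entry into the registry. No other origin is given for treatment comparisons.
- **How exposure is classified.** Follow-up is split into intervals by current treatment status, and "Immortal-time bias will be addressed by classifying all person-time prior to treatment initiation as unexposed". Switching opens a new interval, and stopping returns the patient to the unexposed state.
- **What is adjusted for.** Regression and propensity matching or weighting are planned, and "the a priori covariate set includes age, sex, subtype", followed by baseline stage or organ involvement and key comorbidities.
- **How robustness is judged.** Landmark analyses at 6 and 12 months classify patients by treatment status at the landmark. Agreement with the main result is to be read as a sign of robustness.
- **How treatment is chosen.** In the case conference described under Study setting, a confirmed diagnosis leads to "treatment as well as follow-up procedure depending on the respective diagnosis decided".

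**The concern.** The immortal-time rule is sound for its own purpose, but it acts only on time observed before a patient starts treatment. A patient who started before enrolment has no such time in the registry. That patient enters as exposed on day one, selected for having lived, and stayed on treatment, until enrolment. Patients who started elsewhere and died before they could be referred contribute nothing. If risk varies between patients in ways the covariates do not capture, the treated group is enriched with lower-risk survivors and the treatment looks better than it is.

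The stated robustness criterion makes this worse. The landmark groups contain the same prevalent users, so both analyses can carry the same bias and agree. A reader would take that agreement as reassurance.

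Subtype raises a second, conditional problem. If a therapy is used in one subtype only, patients of other subtypes have a propensity of zero. Weighting or matching across subtypes is then undefined, and regression has to extrapolate.

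**Working it through.** **The plan's own figure.** The only design calculation is a 95% half-width of about 6% for a 10% event rate at N of about 100–150. 1.96 × √(0.1 × 0.9 / 100) = 5.9%, and at N = 150 it is 4.8%, so the figure reproduces at the lower end. It concerns a single proportion and says nothing about treatment comparisons.

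**Tracing three patients through the stated rules.**

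1. Enrolled when suspected, treatment starts later: time before the start is unexposed, time after is exposed. Handled correctly.
2. Enrolled on treatment after referral: exposed from time zero. The immortal-time rule has nothing to act on. No delayed entry, and no covariate for time on treatment or since diagnosis, is stated.
3. Started treatment elsewhere and died before referral: never enrolled.

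At the landmarks, a surviving patient of type 1 who has started by then and a patient of type 2 who is still on treatment are both classed as treated. Nothing separates them.

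**Illustration of size.** None of these inputs is in the protocol article. Assumed: baseline hazard h = 0.2 per year; gamma frailty with mean 1 and variance θ; half the patients treated; new users start at enrolment; prevalent users start 0–4 years (uniform) before it; untreated patients enter without delay; 5 years of follow-up; no switching or stopping; time measured from enrolment; true HR 1.0.

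With gamma frailty the population hazard at time t is h / (1 + θht). For treated patients who have already survived L years, the apparent HR at time t after enrolment is (1 + θht) / (1 + θh(t + L)). With L = 2:

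- θ = 0.5: 1/1.2 = 0.83 at enrolment, rising to 1.5/1.7 = 0.88 at 5 years.
- θ = 1.0: 1/1.4 = 0.71 at enrolment, rising to 2.0/2.4 = 0.83 at 5 years.
- θ = 0: 1.00 throughout.

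Simulated Cox estimates (400,000 patients per cell, standard error of the log HR about 0.004–0.005), by share of treated patients who start before enrolment:

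| θ | 0% | 30% | 60% | 100% |
|---|---|---|---|---|
| 0 | 1.00 | 1.00 | 1.00 | 1.00 |
| 0.5 | 1.00 | 0.96 | 0.93 | 0.87 |
| 1.0 | 1.01 | 0.95 | 0.89 | 0.80 |

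The 100% column lies within the ranges from the formula. Shares are counted before those who die prior to enrolment drop out. For θ = 0.5, average survival over the 0–4 year delay is (1/4) × 10 × (1 − 1/1.4) = 0.714, so 30% becomes 0.3 × 0.714 / (0.3 × 0.714 + 0.7) = 23% of treated patients actually enrolled, and 60% becomes 52%.

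With a true HR of 0.7, the estimate moves from 0.74 (0% prevalent) to 0.70 (60%) at θ = 0.5, and from 0.77 to 0.69 at θ = 1.0. The relative shift is similar.

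**Subtype.** Let P be the probability of receiving therapy A given covariates that include subtype. If A is given only in subtype s, then P = 0 in every other subtype, and no weight or match exists there. Within s, overlap is not ruled out. The text states neither a within-subtype restriction nor an overlap check.

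**The case against.** **This may be detail left to fuller or question-specific plans.** The article foresees sub-studies and separate publications, and the list of covariates is informed by causal diagrams for each question. That carries some weight. But the article itself fixes the exposure rule, the covariate set, the sensitivity analyses and the criterion for robustness. The point is about what those rules do when followed.

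**The estimates are already labelled exploratory, not causal, and comparative effectiveness is not a primary endpoint.** True, and this limits the severity. The reasons given for the label are imprecise dates and visit timing, however. Survivor selection is a different problem and is not mentioned.

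**The direction is not certain.** Untreated comparators may also be long-diagnosed survivors, or carriers of a genetic variant who are at low risk. This stands. The illustration assumes comparators who enter without delay, and the net bias could be smaller or reversed.

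**Stronger readings a reader might infer.**

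- That the plan compares treatments across subtypes and so has no propensity overlap. The text does not say that subtypes will be pooled for a comparison, and an analysis confined to ATTR could still use subtype as a covariate. Nor does it say that therapies are mutually exclusive; the Introduction says only that therapeutic considerations differ.
- That early deaths and early stoppers are never seen. Suspected cases are enrolled and can be followed from before treatment, and surviving stoppers remain eligible.
- That the spurious benefit is about 13 percentage points. With an assumed Weibull shape of 0.6 and 60% two-year survival, S(3)/S(1) = 0.73 against 0.60. That compares a wholly prevalent treated group with a wholly new untreated group, without adjustment. It is a worst case, not an estimate for this registry.

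**Conclusion.** The point holds as a design weakness of unknown size. The stated origin, exposure rule and covariate set leave prevalent-user bias unaddressed, and the landmark comparison cannot detect it because it mixes the same patients. Under the assumptions shown, a null treatment would appear with an HR of about 0.96 to 0.89 when 30–60% of treated patients started before enrolment. With no unmeasured heterogeneity the bias vanishes. The protocol article gives neither the prevalent share nor the heterogeneity, so these figures show what is possible and do not predict the result.

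The subtype part is conditional: positivity fails for a therapy confined to one subtype if subtypes are pooled, and the plan states nothing that prevents it. The exploratory label keeps the matter at the level of something that should be changed rather than a fatal flaw.

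**What to change.** In the Statistical analysis plan:

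1. Make the main comparison among patients untreated at enrolment: those who then start treatment and their untreated comparators. Define untreated as never having received the treatment under study, because a patient who stopped before enrolment would otherwise count as unexposed.
2. Include already-treated patients only in a sensitivity analysis with delayed entry, on a time scale from treatment start or diagnosis.
3. Add time since diagnosis to the covariate set.
4. Run the 6- and 12-month landmark analyses separately in new users, and limit the robustness statement to immortal time.
5. Compare treatments within subtype, or use subtype as a Cox stratum where survival models are pooled. Fit propensity models within subtype, report overlap and trim to it.
6. Report, by subtype, how many patients were untreated and how many already treated at enrolment.

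The cost is mainly wording, since therapy is already among the items recorded at registration. The real price is a smaller main comparison. Study status reports 849 patients enrolled by 31 March 2026, against the 100–150 anticipated in the Statistical analysis plan. That total spans all subtypes and may include suspected cases and carriers, so it does not show that the new-user sample within each subtype is large enough. Item 6 would settle this.
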